### Sample Size

As the intervention concerns an innovative treatment, the study is primarily aimed at studying acceptability and feasibility. For this goal, a power calculation cannot be performed.

To explore noninferiority of eCBT to traditional CBT (as delivered in the NordLOTS), we will use a historical control design. A power calculation (noninferiority margin set at 4 points on the CY-BOCS) shows that 21 participants per treatment arm would be sufficient to show noninferiority (80% power).

## Results

The study has been approved by the Regionale komiteer for medisinsk og helsefaglig forskningsetikk (REK 2016/716/REK nord) and has been registered in the ISRCTN registry (ID: ISRCTN37530113). The study will be conducted according to the principles of the Declaration of Helsinki (version October 19, 2013; WMA, 2013) [51] and in accordance with the Medical Research Involving Human Subjects Act (WMO) and Good Clinical Practice (GCP) standards.

Multimedia Appendix 5 provides a summary of the trial registration data. Informed consent will be obtained prior to enrollment in the study. Inclusion started on September 04, 2017. Data collection is ongoing. The results will be published in peer-reviewed academic journals, presented at scientific conferences, and communicated to the participants and patient organizations. International Committee of Medical Journal Editors (ICMJE) criteria on contributorship and authorship are applied.

## Discussion

This study is the first step in testing the acceptability, feasibility, and preliminary effectiveness of eCBT. In case of positive results, future steps include improving the eCBT treatment package based on feedback from service users, examining cost-effectiveness in a randomized controlled trial, and making the package available to clinicians and other service providers treating OCD in children and adolescents.

Although eCBT has not been developed with the intention to overcome all barriers to treatment, we aim to improve treatment response by offering a more focused application of CBT principles in a user-friendly way. A future step would be to examine which approach works best for which patients.

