## Abstract

**Background:**

Although the evidence base of cognitive behavioral therapy (CBT) for pediatric obsessive-compulsive disorder (OCD) has been broadly established, the treatment is hampered by limited access, poor compliance, and nonresponse. New technologies offer the opportunity to improve the accessibility, user friendliness, and effectiveness of traditional office-based CBT. By employing an integrated and age-appropriate technologically enhanced treatment package, we aim to execute a more focused and attractive application of CBT principles to increase the treatment effect for pediatric OCD.

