**Objective:**

The aim of this open study is to explore the acceptability, feasibility, and effectiveness of a newly developed enhanced CBT (eCBT) package for pediatric OCD.

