Several types of technology-based CBT (tCBT) programs for OCD have been developed and implemented, including online bibliotherapy, online self-help therapy, therapist-supported computerized CBT, smartphone apps, traditional CBT delivered via telephone or videoconferencing, and combinations of these forms [22,24-27]. Preliminary evidence shows that these programs yield positive effects overall. A meta-analysis on tCBT for OCD, which was based on eight randomized controlled trials (N=420, including youth, n=31), showed a large effect size for tCBT (*d*=1.18, CI 0.80-1.56) [25]. Moreover, tCBT was found to be superior to control conditions (waitlist and active controls, *d*=0.82), and no difference was found in efficacy between tCBT and traditional therapist-delivered CBT [25]. Results from a recent systematic review on tCBT for pediatric OCD (N=96) indicated that tCBT can be a feasible and acceptable treatment for youth with OCD [24].

However, tCBT for OCD is still in its infancy. Current evidence is limited by small numbers of trials, small sample sizes, methodological shortcomings, and focus on adults in most studies. In addition, tCBT programs vary greatly in format, duration, intensity, length, and their specific aims, making it hard to draw firm conclusions. This stresses the need for further research, especially in children with OCD.

In this protocol, we propose an *enhanced* cognitive behavioral therapy (eCBT) package for pediatric OCD, integrating modern internet technology and traditional CBT, in order to improve treatment response as well as user friendliness.

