### Aims and Hypotheses

The aim of the study is to explore whether eCBT is (1) a feasible intervention in terms of treatment drop out; (2) an acceptable intervention; and (3) an effective intervention for children and adolescents with OCD in terms of positive treatment outcomes and showing noninferiority to traditional CBT (Nordic Long-term OCD Treatment Study [NordLOTS]) [11] for the primary outcome measure (Children’s Yale-Brown Obsessive-Compulsive Scale [CY-BOCS]).

We hypothesize that (1) preterm treatment drop out will be equivalent or lower than that found for traditional CBT (≤10%) [11]; (2) eCBT will be positively evaluated by children and their parents; (3) there will be a considerable reduction in OCD symptoms after treatment; and (4) the treatment outcome (CY-BOCS) for eCBT will show noninferiority to traditional CBT (NordLOTS) [11].

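### The package is meant to increase the treatment effect, but on the CY-BOCS the plan hypothesizes only noninferiority, and its t test is tied neither to the 4-point margin nor to a superiority claim

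*Protocol article*

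**What the plan says.** **Purpose of the package.** Three places name a larger effect. The Abstract (Background) says "we aim to execute a more focused and attractive application of CBT principles to increase the treatment effect for pediatric OCD". The Introduction (Background) proposes the package "in order to improve treatment response as well as user friendliness". The Discussion says "we aim to improve treatment response by offering a more focused application of CBT principles in a user-friendly way".

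**Aim of the study.** This is narrower. The Abstract (Objective) is to "explore the acceptability, feasibility, and effectiveness of a newly developed enhanced CBT (eCBT) package for pediatric OCD". Aims and Hypotheses defines effectiveness as positive outcomes plus noninferiority to NordLOTS on the CY-BOCS. Sample Size adds that "the study is primarily aimed at studying acceptability and feasibility".

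**Hypotheses.** There are four:
- Hypothesis 1 compares drop out with traditional CBT: "preterm treatment drop out will be equivalent or lower than that found for traditional CBT (≤10" percent).
- Hypothesis 2 expects a positive evaluation by children and parents.
- Hypothesis 3 is within-group: "there will be a considerable reduction in OCD symptoms after treatment".
- Hypothesis 4 is the comparison on symptoms: "the treatment outcome (CY-BOCS) for eCBT will show noninferiority to traditional CBT (NordLOTS").

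**Analysis.** Statistical Analysis plans an independent t test of the before-after CY-BOCS difference against the result reported for NordLOTS. It mentions no margin. The margin of 4 points appears only under Sample Size, with 21 per arm for 80% power. The planned eCBT group is 30.

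**The concern.** A package built to raise the treatment effect invites the question whether it does so. No hypothesis asks that on the CY-BOCS. Hypothesis 3 has no comparator, and hypothesis 4 asks only whether eCBT is not too much worse.

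The named test does not close the gap. Without further instruction, an independent t test gives a p value against a difference of zero. That p value does not answer hypothesis 4, which needs a comparison with the margin. Nor does any hypothesis give it a role as evidence of superiority. After the data are in, a significant result in favour of eCBT would be an unplanned claim, and a nonsignificant one could be misread as support for noninferiority.

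What is at stake is the wording of the conclusion. Both the Abstract and the Discussion make next steps depend on positive results, including making the package available to clinicians. It should be settled beforehand which result supports which statement.

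**Working it through.** **Inputs from the article:** margin 4 points; 21 per arm; 80% power; planned eCBT n = 30.

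**Assumptions, because the article does not state them:** one-sided alpha 0.025 or 0.05; true difference 0 in the power calculation; common SD of change; control-group size, taken as 30 to 300. Below, the difference is mean improvement with eCBT minus mean improvement in NordLOTS, so positive values favour eCBT and the margin lies at −4.

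**Step 1: the plan's own figure.** With n per arm = 2·SD²·(z₁₋α + z₀.₈₀)²/4², the SD at which n is exactly 21 is 4·√(21/2)/(z₁₋α + z₀.₈₀).
- One-sided 0.025: 12.96/(1.960 + 0.842) = 4.63. The SD at which n is exactly 20 is 4.51, so 21 corresponds to an SD of about 4.51 to 4.63.
- One-sided 0.05: 12.96/(1.645 + 0.842) = 5.21, so the SD is about 5.09 to 5.21.

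The figure of 21 cannot be strictly reproduced without the SD and alpha, but it is attainable with these SDs. I use 4.57 as the central value at one-sided 0.025 and 9 as a pessimistic value. An SD of 9 does not fit 21 per arm and serves only to show sensitivity.

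**Step 2: what each conclusion requires of the observed difference.** SE = SD·√(1/n₁ + 1/n₂). Noninferiority passes if the observed difference exceeds −4 + t·SE. Superiority passes if it exceeds t·SE. Here t is the 97.5% quantile, so both are read from the same 95% CI.

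| SD | n₁ vs n₂ | SE | t·SE | Noninferiority needs more than | Superiority needs more than |
|---|---|---|---|---|---|
| 4.57 | 30 vs 30 | 1.18 | 2.36 | −1.64 | 2.36 |
| 4.57 | 30 vs 300 | 0.875 | 1.72 | −2.28 | 1.72 |
| 9 | 30 vs 30 | 2.32 | 4.65 | +0.65 | 4.65 |
| 9 | 30 vs 300 | 1.72 | 3.39 | −0.61 | 3.39 |

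With an SD that fits the stated sample size, eCBT can pass while observed 1.6 to 2.3 points worse. With SD 9 and 30 versus 30 the direction reverses, and eCBT must be observed at least 0.65 points better to pass.

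**Step 3: power to show improvement** (noncentral t, two-sided 0.05).

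| SD | n₁ vs n₂ | True gain 2 points | True gain 4 points |
|---|---|---|---|
| 4.57 | 30 vs 30 | 38% | 92% |
| 4.57 | 30 vs 300 | 63% | above 99% |
| 9 | 30 vs 30 | 13% | 39% |
| 9 | 30 vs 300 | 21% | 64% |

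For 80% power at a true gain of 2 points and SD 4.57, n per arm = 2·4.57²·(1.960 + 0.842)²/2² ≈ 82.

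**Step 4: the passages side by side.** The purpose statements need evidence that the difference is above 0. Hypothesis 4 needs evidence that it is above −4. Statistical Analysis names a test whose usual null value is 0 and gives no rule for either statement.

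**The case against.** The strongest reply is that the purpose of a package is not the question of its first study. The Abstract, the Aims and the Sample Size section consistently describe an exploratory study of feasibility, acceptability and noninferiority, and the Discussion calls it a first step on preliminary effectiveness. A rationale broader than the hypotheses is normal. Access and user friendliness are also stated goals, and being more accessible without being materially worse is a standard reason for a noninferiority question. This stands, and it rules out several stronger readings that a reader might infer:

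- *The study never answers its own question.* Not supported. The question it sets itself is addressed; improved response is the package's goal, not a study hypothesis.
- *Noninferiority is the only comparative hypothesis.* Not supported. Hypothesis 1 also compares drop out with traditional CBT. The statement is true only for the CY-BOCS.
- *Passing while observed worse is a defect of this plan.* Not supported. It is a property of every noninferiority test.
- *The authors intend to report noninferiority as enhancement.* No passage says so.

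A second reply is that a superiority step would rest on an unrandomized historical comparison with low power. That is a reason for caution in wording. It does not count against the ordered reading in particular, since the noninferiority claim already planned uses the same control. A third is that an article may leave a test sequence to the full plan. That excuses the missing detail, but the article does name its test and hypotheses, and as written they do not match.

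**Conclusion.** The point holds as a mismatch between rationale, hypothesis and named analysis. Noninferiority on the CY-BOCS cannot by itself support a statement that eCBT improves response, and the t test as described is linked neither to the margin nor to superiority. The study's narrower aims are not undermined.

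The size is conditional. At SD 4.57 and two-sided 0.05, an improvement claim needs eCBT observed about 1.7 points better (300 controls) to 2.4 points better (30 controls), while noninferiority tolerates a deficit of 2.3 to 1.6 points. Power for a true 2-point gain is 38% with 30 versus 30, 63% with 300 controls, and 13% at SD 9 with 30 versus 30. SD, alpha and control-group size are all assumptions. The mismatch itself does not depend on them. This is an inexpensive improvement worth making, not a fatal flaw.

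**What to change.** In Aims and Hypotheses and in Statistical Analysis:

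1. Report one 95% CI for the eCBT minus NordLOTS difference in CY-BOCS change, with its direction defined.
2. Test noninferiority first: the CI must exclude a deficit of 4 points or more. Only if this is met, test superiority: the CI must exclude zero in favour of eCBT. The fixed order needs no alpha adjustment.
3. State that step 1 alone supports only the conclusion that eCBT is not worse by more than 4 points. Any statement of improved response requires step 2 and remains preliminary, because the control is historical and not randomized.
4. State that power for modest gains is low, giving the SD and control-group size used.

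The cost is a few sentences, with no new patients, data or alpha. The downside is that a result that is only noninferior can no longer be described as enhancement. A smaller alternative is one sentence saying that noninferiority will not establish improved response, but this would leave the t test unconnected to the margin.

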## Appendix

Multimedia Appendix 1 Overview of the app system.

Multimedia Appendix 2 Psychoeducation tool: stories.

Multimedia Appendix 3 Questions for monitoring treatment progress via the app system.

Multimedia Appendix 4 Enhanced cognitive behavioral therapy: treatment overview.

Multimedia Appendix 5 Summary of trial registration data.

## Abbreviations

BTPS: Barriers to Treatment Participation Scale
CBCL: Child Behavior Checklist
CBT: cognitive behavioral therapy
CGAS: Children’s Global Assessment Scale
CGI-I: Clinical Global Impressions Scale-Improvement
CGI-S: Clinical Global Impressions Scale-Severity
COIS-R: Child Obsessive-Compulsive Impact Scale-Revised
CSQ-8: Client Satisfaction Questionnaire-8
CY-BOCS: Children’s Yale-Brown Obsessive-Compulsive Scale
eCBT: enhanced cognitive behavioral therapy
ERP: exposure with response prevention
FAS-SR: Family Accommodation Scale for OCD–Self-Rated Version
K-SADS-PL: Schedule for Affective Disorders and Schizophrenia for School-Age Children Present and Lifetime Version
MFQ: Mood and Feelings Questionnaire
OCD: obsessive-compulsive disorder
SCARED-R: Screen for Child Anxiety-Related Emotional Disorders-Revised
SDQ: Strengths and Difficulties Questionnaire
tCBT: technology-based cognitive behavioral therapy
TiC-P: Trimbos/iMTA Questionnaire for Costs associated with Psychiatric Illness
UEQ: User Experience Questionnaire
YSR: Youth Self-Report Questionnaire
